### Double blinding

2.6

This study is double-blinded. According to the allocation scheme, subjects will receive an intravenous infusion of S-ketamine or 0.9% saline during the procedure and a continuous infusion of S-ketamine or 0.9% saline via patient-controlled intravenous analgesia (PCIA) device after surgery. To ensure that the investigators are blinded, the drug administrator ([name], [name]) will prepare two 20 mL syringes (Weigao Group Medical Polymer Products Co., Ltd.) in a separate room filled with S-ketamine at a concentration of 2.0 mg/mL or 0.9% normal saline. The drug administrator will also configure the PCIA device according to the allocation scheme of the subject. The syringes and the PCIA device will look the same. The drug administrator will not be involved in other parts of the trial. Nurses, surgeons, anesthesiologists, outcome assessors, and statistical analysts will be blinded to the subject’s group and intervention throughout the trial. An independent data and safety monitoring board will oversee the practice and will not disclose the allocation group of the subjects until statistical analysis is completed. In an emergency (such as rapid deterioration of the patient’s clinical status), the anesthesiologist may request disclosure of the intervention the subject received or adjust or interrupt the study drug infusion if necessary, which will be documented. Unblinded subjects will be included in the intention-to-treat (ITT) analysis but excluded from the per-protocol (PP) analysis.

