The choice of S-ketamine dose and mode of administration was based on published clinical trials and drug manufacturer instructions. S-ketamine is twice as potent in analgesia as ketamine, and the same anesthetic effect can be achieved with a dose of 1/2 ketamine. A subanesthetic dose of S-ketamine (0.25 mg/kg) was often selected by the investigator for the prevention of POD or perioperative neurocognitive dysfunction (Wei et al., 2022; Han et al., 2023; Ma et al., 2023). However, we need to be clear that a dose of 1/2 ketamine may not be equivalent to the dose at which S-ketamine exerts neuroprotective effects, and that relatively high doses of S-ketamine are more prone to adverse events and potential safety concerns (McIntyre et al., 2021). Subjects will receive intraspinal anesthesia rather than general anesthesia in this study, which avoids the influence of other anesthetic drugs on the neuroprotective effects of S-ketamine. In addition, elderly patients with preoperative dementia, depression, and multiple comorbidities will be included, making the dose of S-ketamine received in the intervention group more conservative. Our previous study found that subjects receiving 0.3 mg/kg/h S-ketamine had hallucinations and dreaminess, although this dose was subanesthetic (Zhu et al., 2023). Therefore, we will use a smaller subanesthetic dose of S-ketamine 0.2 mg/kg infused over 1 h in this trial. In antidepressant therapy, the short-term efficacy of intravenous ketamine necessitates repeated dosing in most cases to maintain therapeutic benefit. Therefore, the intervention group will receive an intravenous infusion of 0.010 mg/kg/h for 48 h via the PCIA device after surgery, a dose with fewer psychiatric side effects and maintaining the need for analgesia.

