### Trial safety

2.12

The study team will give the subjects or their designated agents a complete and comprehensive introduction to the study objectives, study procedures, investigational drugs, reasonably expected benefits, possible toxicities, and the risks of participating. Written informed consent will be obtained from all subjects to protect their legitimate rights and interests. The study team must improve an emergency plan before the start of the trial. This will involve communication with multiple disciplines to inform them of the possible adverse events that may occur during this clinical study and to obtain their assistance in case of an emergency. The dose and concentration of S-ketamine that will be received by subjects in this trial were selected based on the pharmacokinetics, pharmacodynamics, published clinical trials, and recommendations from the drug’s manufacturer. Interventions for tachycardia, bradycardia, hypotension, and hypertension include adjustment of the study drug infusion, administration of vasoactive agents, or both. Interventions for hypoxemia include oxygen administration or physical therapy. Management of subjects with POD should first include identifying and correcting the underlying etiology, including the immediate exclusion of life-threatening causes such as hypoxia, hypotension, hypoglycemia, and sepsis. Non-pharmacologic treatment is the first-line treatment strategy. Haloperidol will be administered to subjects with severe agitation (RASS score of +3 or greater) who fail to respond to non-medical therapy. The study team will treat or rescue drug-induced adverse reactions such as nausea, vomiting, and anaphylactic shock according to established standard operating procedures. The investigators involved in this trial have extensive clinical experience, are good at handling acute and critical events, and have received professional Good Clinical Practices (GCP) training. The multifunction monitor will monitor the subject during the procedure and in the PACU. Subjects will be monitored continuously in the surgical ward for at least 24 h using ECG, blood oxygen levels, and blood pressure.

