### Adverse events reporting

2.13

Adverse events (AE) refer to all untoward medical events that occur after the subject receives the investigational product. These include symptoms, signs, diseases, or laboratory abnormalities but may not necessarily have a causal relationship with the investigational product. The investigator should record and report all AE that are directly observed or spontaneously written by the subject in concise language. In addition, subjects should be asked about AE from the beginning to the end of the trial. AE should be recorded on the designated Adverse Event Form. The severity of AE will be judged according to standard adverse reaction evaluation criteria. All AE will be handled according to the standard operating procedures for handling adverse reactions that were developed by the clinical trial center. The AE record form shall be truthfully filled in, including the occurrence time, severity, duration, measures taken, and outcome of the AE.

A serious adverse event (SAE) refers to death or a life-threatening event, permanent or severe disability or loss of function, hospitalization or prolongation of hospitalization, a congenital anomaly or disability, or any other important medical events experienced by the subject after receiving the investigational product. Any subject with SAE should be withdrawn from the trial, and the investigator should actively treat the subject with SAE. The investigator must also complete the SAE Report Form in as much detail as possible, and sign and date it. The investigator should report the SAE to the Principal Investigator ([name]) and the Ethics Committee of Qingdao University within 24 h of being informed of the SAE.

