### Statistical methods

2.16

To analyze the primary study outcome, we will use the ITT analysis set. The ITT analysis set is defined as all subjects who undergo randomization regardless of their intervention. Data processing and analysis will be performed using R version 4.3.0 and the Storm Statistical Platform.^1^ Continuous variables will be tested for normality using Shapiro–Wilk, with normal data expressed as mean ± SD, non-normal data as median and interquartile range, and categorical data as number of cases (n) and percentage (%). For demographic data, baseline characteristics, and intraoperative data, quantitative data between the two groups will be compared using a two-independent sample t-test or Mann–Whitney U test, and qualitative data will be compared using the chi-square test, continuous corrected chi-square test, or Fisher’s exact test. The primary outcome is a dichotomous measure, and the odds ratio (OR) and 95% confidence interval (CI) of the incidence of POD between the intervention and control groups will be calculated using a logistic regression model. This is a pragmatic study, and potential confounding variables may bias the degree of association between interventions and primary outcomes. The logistic regression model will therefore include demographics and baseline characteristics as covariates. We plan to build four different models. Model 1 will only include grouping factors and not control for confounding factors. The net OR and 95% CIs will be calculated. Model 2 will adjust for sex, age, ASA classification, comorbidities, and education level. Model 3 will adjust for electrolyte abnormalities, hypoproteinemia, and anemia based on Model 2. Model 4 will adjust for smoking, alcohol use, history of falls, vision or hearing abnormalities, preoperative dementia, depression, functional status, frailty, sleep disorders, and aCCI based on Model 3. Adjusted OR and 95% CIs will be calculated from Models 2, 3, and 4. We will perform a sensitivity analysis on the primary outcome to compare the effects of different analysis sets (ITT and PP) and statistical methods (modified Poisson regression and logistic regression) on the robustness of the primary outcome. The PP analysis set excludes subjects who did not meet our eligibility criteria or had incomplete adherence to the trial medication. Subgroup analyses will be performed for age, gender, dementia, depression, frailty, sleep disorders, vision or hearing abnormalities, and functional status, and interactions will be investigated.

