
We will only use the PP analysis set to evaluate our secondary outcomes. Our secondary outcomes are exploratory, and no adjustment for type I errors will be made for multiple comparisons. The ordered multiclass (number of POD episodes) and disordered multiclass (subtype of POD) variables will be analyzed using the Mann–Whitney U test, chi-square test, or Fisher’s exact test. Quantitative data (onset and duration of POD, delirium severity score, time to discharge criteria, and length of stay) will be analyzed using the Mann–Whitney U test, and pseudo-median difference and 95% CIs will be estimated using the Hodges-Lehmann method. Time to first pump compression is survival data and will be analyzed using the Kaplan–Meier survival curve and log-rank tests. Hazard ratios (HR) and 95% CIs will be calculated using a one-way COX regression. NRS scores, opioid consumption, and sleep quality at different time points after surgery are repeated measures data and will be analyzed using generalized estimating equations. The difference and 95% CIs will be calculated. Analysis of covariance (ANCOVA) will be used to compare between-group differences in the Timed Up and Go test, active range of motion of the affected knee or hip, and BI score, adjusting for covariates (baseline measurements), and estimating least square mean (LSM) differences and 95% CIs. Safety indicators will be analyzed using the Safety Analysis Set, which will include all randomized subjects who received at least one dose of medication. All statistical tests will be two-sided. *p* < 0.05 will be considered statistically significant.

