### Missing data

2.17

Missing data in the ITT analysis set will be handled using the multiple imputation method, with the number of imputations set to 5 and the maximum number of iterations set to 50. Continuous variables will be imputed using a predictive mean-matching model, and categorical variables will be imputed using a logistic regression model.

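### Secondary outcomes are to be analysed only in the per-protocol set, whose membership depends on post-randomisation events, and no intention-to-treat result is planned to check them

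*Protocol article*

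**What the plan says.** Section 2.16 (Statistical methods) uses the ITT set, meaning everyone randomised, for the primary outcome and adds a PP analysis as a sensitivity check. For the secondary outcomes it says: "We will only use the PP analysis set to evaluate our secondary outcomes". The same section calls these outcomes exploratory and applies no multiplicity adjustment. It nevertheless plans effect estimates, 95% confidence intervals and two-sided tests at 0.05.

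Membership of the PP set is described in two places:

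- Section 2.16: "The PP analysis set excludes subjects who did not meet our eligibility criteria or had incomplete adherence to the trial medication".
- Section 2.6 (Double blinding): "Unblinded subjects will be included in the intention-to-treat (ITT) analysis but excluded from the per-protocol (PP) analysis".

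Three further passages describe events that may bear on membership or on follow-up:

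- Section 2.6: "In an emergency (such as rapid deterioration of the patient’s clinical status), the anesthesiologist may request disclosure of the intervention the subject received". The same sentence allows the infusion to be adjusted or interrupted.
- Section 2.12 (Trial safety): interventions for tachycardia, bradycardia, hypotension and hypertension "include adjustment of the study drug infusion, administration of vasoactive agents, or both".
- Section 2.13 (Adverse events reporting): "Any subject with SAE should be withdrawn from the trial".

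Safety indicators are analysed in a separate Safety Analysis Set. On missing values, section 2.17 says: "Missing data in the ITT analysis set will be handled using the multiple imputation method". It does not mention the PP set.

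**The concern.** Randomisation makes the two arms comparable as assigned. An analysis that drops patients because of what happened after assignment keeps that comparability only if the dropped patients are alike, and equally frequent, in both arms. Here there is reason to doubt this. Unblinding is tied to clinical deterioration, and adherence can depend on how the drug is tolerated. The team also reports from its own earlier work that "subjects receiving 0.3 mg/kg/h S-ketamine had hallucinations and dreaminess". The present trial uses a lower rate, but drug-related intolerance remains foreseeable.

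The affected outcomes include results that readers will treat as evidence of efficacy. The Discussion already expects lower pain scores and opioid consumption with S-ketamine. Because the PP set is the only one named, no as-randomised result would stand beside these estimates. The choice also reverses, without a stated reason, the order used for the primary outcome, in a placebo-controlled trial that calls itself pragmatic and claims external validity.

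**Working it through.** **1. Is exclusion a post-randomisation event?**

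| Event | Where | Removed from PP? |
|---|---|---|
| Unblinding, for example on rapid deterioration | 2.6 | Yes, explicit |
| Incomplete adherence to study medication | 2.16 | Yes, explicit |
| Infusion adjusted or interrupted by the clinician | 2.6, 2.12 | Not stated; possible if counted as incomplete adherence |
| Withdrawal after a serious adverse event | 2.13 | Not stated; may also end data collection |

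The first two rows are enough to make the PP comparison non-randomised.

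**2. Which outcomes are affected?** Pain, opioid use, sleep, time to first pump use, Timed Up and Go, range of motion, Barthel index, time to discharge criteria and length of stay can be defined in every patient. For these, an ITT analysis gives a randomised comparison. Onset, duration, severity and subtype of delirium exist only in patients who become delirious (section 2.11.2), so changing the analysis set does not make them randomised comparisons. The Abstract lists safety outcomes among the secondary outcomes, but section 2.16 gives them their own set.

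**3. How large could the bias be?** The plan states no figure to reproduce on this point. The only input from the article is 186 patients per arm (section 2.3). The rest is assumed: a continuous outcome with SD 1, no true effect, excluded fractions e1 (S-ketamine) and e0 (control), and excluded patients worse than their whole-arm mean by d SD.

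- Bias (absolute) = d × [e1/(1 − e1) − e0/(1 − e0)]
- n1 = 186(1 − e1), n0 = 186(1 − e0), SE = √(1/n1 + 1/n0)
- Type I error = 1 − Φ(1.96 − bias/SE) + Φ(−1.96 − bias/SE)

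Worked case, 15% versus 5%, d = 1: bias = 0.15/0.85 − 0.05/0.95 = 0.1765 − 0.0526 = 0.124 SD; n1 = 158.1, n0 = 176.7; SE = 0.1095; bias/SE = 1.13; type I error = 20.5%.

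| Excluded, S-ketamine vs control | d = 0.5: bias, type I error | d = 1: bias, type I error |
|---|---|---|
| 5% vs 2% | 0.016 SD, 5.3% | 0.032 SD, 6.1% |
| 10% vs 3% | 0.040 SD, 6.6% | 0.080 SD, 11.6% |
| 15% vs 5% | 0.062 SD, 8.7% | 0.124 SD, 20.5% |
| 5% vs 5% | 0, 5.0% | 0, 5.0% |

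The result depends on how the deficit is measured. If d is the gap between excluded and retained patients, the bias is d × (e1 − e0). For 15% versus 5% at d = 1 that is 0.10 SD, with a type I error of 15.0%.

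With the arms swapped (5% versus 15%) the bias has the same size and works against S-ketamine. With ITT and complete data it is zero.

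**The case against.** The best defence is that little hangs on these analyses. The secondary outcomes are declared exploratory, the primary outcome is analysed by ITT, and safety has its own set. This stands, and it limits the severity. It does not justify PP as the sole set: the exploratory label deals with multiplicity, not with bias.

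Several stronger readings are tempting, and the article does not support them.

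- *PP removes everyone whose infusion was changed.* Section 2.16 says only incomplete adherence. A clinician-ordered adjustment is permitted by the protocol and is nowhere classed as non-adherence.
- *The bias favours S-ketamine.* It would if more patients, or sicker ones, left that arm. But haemodynamic events can occur in both arms under intraspinal anaesthesia, the anaesthesiologists are blinded, and control patients can also leave through poor compliance or refusal (section 2.2.3). The direction cannot be derived.
- *The PP analyses are complete-case.* Section 2.17 is silent on PP. The generalised estimating equations for pain, opioid use and sleep can use all available visits, and the survival methods for pump use handle censoring.
- *Outcomes are collected on excluded patients anyway.* Follow-up after withdrawal is not described.
- *PP is what costs every secondary comparison its randomised basis.* For onset, duration, severity and subtype, restriction to delirious patients does so already.

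**Conclusion.** The point holds as a should-fix. As written, the plan yields only non-randomised comparisons for pain, opioid use, sleep, pump use, function, time to discharge criteria and length of stay, and provides no ITT result to test them against. The bias could go either way. On the assumed scenarios it is about 0.02 to 0.12 SD, with a type I error of about 5% to 20%; the upper end needs both a 10-point difference in exclusions and a full 1 SD deficit. If few patients are excluded, or if those excluded are alike and equally frequent in the two arms, the effect is negligible. The exclusion rates and deficits are assumptions, not figures from the article. The primary and safety conclusions are not touched.

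**What to change.** In section 2.16, make the ITT set, analysed as randomised, the main set for the secondary outcomes, and keep PP as a sensitivity analysis. In section 2.17, extend the multiple imputation to these outcomes. State in advance whether an infusion adjusted or interrupted by the clinician counts as incomplete adherence for PP membership. Report delirium onset, duration, severity and subtype as descriptive results among delirious patients.

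The cost is a few sentences and no change in sample size: all 186 + 186 = 372 randomised patients stay in the comparison. There are two drawbacks. Outcomes missing after withdrawal (sections 2.2.3 and 2.13) would have to be imputed, so the ITT results rest partly on the imputation model. The estimated effects may also be slightly smaller than under PP. The change should be made before unblinding, so that the choice of set cannot look data-driven.

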### Missing data

2.17

Missing data in the ITT analysis set will be handled using the multiple imputation method, with the number of imputations set to 5 and the maximum number of iterations set to 50. Continuous variables will be imputed using a predictive mean-matching model, and categorical variables will be imputed using a logistic regression model.

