### Sample size calculation

2.3

The sample size for this trial is based on the incidence of POD. A previous meta-analysis reported a 17% incidence of POD in patients who underwent a total joint arthroplasty (Scott et al., 2015). When considering the potential effect of the study intervention, we used the absolute risk reduction of 10% (corresponding to a number needed to treat of 10 patients) recommended by previous studies (Avidan et al., 2017). We therefore assumed that the incidence of POD in the intervention group would be 7%. We used Power Analysis and Sample Size version 15.0 (Stata Corp. LP, College Station, TX, United States) to calculate a sample size of 166 per group. Considering a 10% lost to follow-up rate, at least 186 subjects in each group and 372 subjects should be included.

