#### Primary outcome

2.11.1

The primary outcome is the incidence of POD within 3 days of surgery. The initial evaluation of delirium will begin at least 6 h after surgery followed by 2 assessments daily (800–1,000 and 1,600–1,800) for the first 3 days after surgery, with an interval of at least 6 h between evaluations. Delirium will be assessed using the Chinese version of 3D-CAM (Marcantonio et al., 2014) in addition to medical records over the previous 24 h, nursing records, and discussions with family members.

The 3D-CAM identifies delirium through a diagnostic algorithm based on the four essential features of delirium: (A) acute changes or fluctuations in mental status; (B) inattention; (C) disorganized thinking; and (D) altered level of consciousness. Diagnosis of delirium requires criteria A and B and either or both of criteria C and D. The 3D-CAM has a high sensitivity (84–99%) and specificity (90–97%). If the subject is discharged or dies within 3 days, the last delirium assessment will be considered the replacement for any missing data.

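### Five imputations for the primary ITT analysis are efficient and unbiased, but leave avoidable seed-to-seed variation that matters when the p-value is near 0.05

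*Protocol article*

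**What the plan says.** Section 2.16 (Statistical methods) fixes the primary set: "To analyze the primary study outcome, we will use the ITT analysis set". The primary measure is an odds ratio from logistic regression, tested two-sided at 0.05, in four models. The first is unadjusted: "Model 1 will only include grouping factors and not control for confounding factors".

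Section 2.17 (Missing data) states: "Missing data in the ITT analysis set will be handled using the multiple imputation method", "with the number of imputations set to 5" and up to 50 iterations. For a binary outcome such as delirium, "categorical variables will be imputed using a logistic regression model".

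Two other places bear on how much will be imputed. Section 2.3 (Sample size calculation) gives the only missingness figure in the article: "Considering a 10% lost to follow-up rate". Section 2.11.1 (Primary outcome) has a separate rule for some missing assessments: "If the subject is discharged or dies within 3 days, the last delirium assessment will be considered the replacement for any missing data".

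**The concern.** The number of imputations is a stated choice that applies to the primary analysis, so it is not a detail left to an analysis plan that is not shown. The usual defence of five imputations is relative efficiency, which compares the expected variance with that from infinitely many imputations. It does not say how far the estimate and p-value from one data set move when the imputation is repeated with another seed. The trial is judged against p < 0.05. If that movement is large compared with the distance of p from 0.05, the reported verdict partly reflects the random-number stream. Raising the number after unblinding would look like choosing a result, so it should be set beforehand.

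**Working it through.** **Inputs from the article.** Control incidence 17%: "A previous meta-analysis reported a 17% incidence of POD in patients who underwent a total joint arthroplasty". Intervention incidence 7%; 166 per group before loss; 10% loss; 186 per group, 372 in total; two-sided 0.05; 5 imputations. Power is not stated; 80% is assumed because it returns the stated size.

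**The plan's own figure.** With mean rate 0.12:

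n = [1.960 × √(2 × 0.12 × 0.88) + 0.842 × √(0.17 × 0.83 + 0.07 × 0.93)]² / 0.10² = (0.901 + 0.382)² / 0.01 ≈ 165 per group, against 166 stated.

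166 / 0.90 = 184.4, so 185, against 186 stated. The figures reproduce to within one subject. A 10% loss from 186 leaves 167 observed and 19 missing per arm.

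**Efficiency.** With 10% of outcomes missing and no covariates, the fraction of missing information (FMI) is about 0.10 to 0.11. Relative efficiency = 1 / (1 + FMI/m) = 1 / (1 + 0.10/5) = 0.98.

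**Movement between seeds.** The standard deviation of the pooled z across seeds is roughly √(FMI/m) = √(0.10/5) = 0.14 for m = 5. Simulation under 7% versus 17% gives 0.17 for m = 5 and 0.05 for m = 50.

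**One borderline data set** (15/167 versus 28/167, 19 missing per arm). Complete cases: OR = (15/152)/(28/139) = 0.49; SE of the log OR = √(1/15 + 1/152 + 1/28 + 1/139) = 0.341; z = −0.714/0.341 = −2.09; p = 0.036. The rough rule for m = 5 gives |z| between 2.09 − 1.96 × 0.14 and 2.09 + 1.96 × 0.14, that is p of about 0.018 to 0.069. Full simulation (imputation by arm, Rubin's rules, t reference) gives a longer upper tail, because the between-imputation variance is itself poorly estimated from five draws:

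| Imputations | Central 95% of p over seeds | Seeds with p ≥ 0.05 | Central 95% of OR |
|---|---|---|---|
| 5 | 0.018–0.085 | 25–27% | 0.45–0.54 |
| 50 | about 0.030–0.047 | under 1% | not tabulated |
| 100 | about 0.032–0.044 | about 0% | 0.48–0.50 |

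**How wide the exposed zone is.** With 28/167 control events and m = 5, the share of seeds with p < 0.05 is 94%, 74%, 33%, 6.5% and 0.2% for 14, 15, 16, 17 and 18 intervention events. With m = 100, only 16 events remains open (8% of seeds below 0.05).

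**Across trials** (186 per arm, 1,500 simulated trials × 200 seeds, outcomes missing at random, Model 1). Chance that two seeds disagree on p < 0.05:

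| Outcomes missing | m | 7% v 17% | No effect (17% v 17%) | 10% v 17% (assumed) |
|---|---|---|---|---|
| 10% | 5 | 5.7% | 2.1% | 8.5% |
| 10% | 50 | 1.5% | 0.7% | 2.3% |
| 10% | 100 | 1.1% | 0.4% | 1.4% |
| 5% | 5 | 3.3% | 1.5% | 5.5% |
| 3% | 5 | 2.5% | 1.1% | 4.0% |
| 1% | 5 | 1.1% | 0.8% | 2.4% |

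**Error rates.** At 10% missing, rejection under no effect is 5.1% with m = 5 and 5.0% with m = 50. Under 7% versus 17%, power is 79% and 80%. With 1,500 trials the standard errors are about 0.6 and 1.0 percentage points, so neither pair differs meaningfully.

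**The case against.** The example was chosen to lie near 0.05. At the planned rates, 12/167 versus 28/167, complete-case p is 0.009; five imputations give p of about 0.004 to 0.028, and only 0.1 to 0.2% of seeds reach 0.05. This stands: a reader might infer that the seed generally decides the trial, and the figures do not support that.

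The 10% is a recruitment allowance, not a forecast of missing delirium outcomes. Delirium is assessed over only three days, and section 2.11.1 fills gaps after discharge or death with the last assessment. If that rule is applied, the imputed share should fall below 10%; the article does not say by how much, nor how the rule fits with imputation. At about 2% missing (control 31/182), only 18 intervention events is truly open. This also stands, but does not dispose of the point. Withdrawals (section 2.2.3) remain, as do subjects with a serious adverse event, whom section 2.13 has withdrawn. So do subjects randomized on the day of admission (Table 2) who have no postoperative assessment to carry forward. At about 5% missing (17/177 versus 30/177), some 35% of seeds still give p ≥ 0.05 with m = 5, against 3% with m = 100.

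Any finite number leaves some seed dependence. With 16/167 versus 28/167, 16% of seeds fall below 0.05 at m = 50 and 8% at m = 100. This stands, and is why recording the seed belongs with the change.

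A reader might also infer bias or an inflated type I error. Rubin's rules already carry the finite-m penalty, and the simulated error rates show neither. Nor do the documents support a claim that incomplete covariates in Models 2 to 4 make matters worse: the covariates are collected before surgery and no missingness figure is given for them.

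**Conclusion.** The point holds as a minor one. Five imputations are valid and about 98% efficient, but low for a reproducible p-value if missing primary outcomes come near 10%. The verdict is then exposed when p lies roughly between 0.025 and 0.085, and in a narrower zone with less missingness. At 10% missing, two seeds agree in 91 to 98% of simulated trials. These figures assume 80% power in the design, outcomes missing at random and equally in both arms, and the unadjusted Model 1. Auxiliary variables or imputed covariates would change the fraction of missing information in ways the article does not let one quantify.

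**What to change.** In section 2.17, change the number of imputations from 5 to 100 (at least 50), and record the random seed before unblinding. Reporting the Monte Carlo error of the primary odds ratio would let readers see that what remains is small. For 372 subjects the cost is one number in the text and minutes of computing, with no statistical downside. The change narrows the spread between seeds; the recorded seed makes the reported result repeatable.
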